## Objectives

Therefore, the main objectives of this “Physical Activity in TMD (PAT)” study are,To assess the long-term effect of objective physical activity level and sleep duration on clinical characteristics in well-defined TMD patient groups.To analyze the impact of physical activity on treatment response to conventional TMD management approaches by determining the cut-off value for physical activity that affects treatment prognosis.To define the causal relationship between abnormal physical activity levels and sleep durations on chronic, high-intensity TMD pain, its comorbidities, and systemic inflammatory marker levels.

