#### Recruitment of cases

Data will be gathered sequentially from all participants visiting the participating hospital for TMD and provide written informed consent from July 2021. Recruitment will proceed for 12 months and may be prolonged when the number of cases is insufficient. The final sample size is estimated to be approximately 200 participants based on a previous study on rheumatoid arthritis using statistical sample size estimation methods (α = 0.05, β = 0.10) [11].

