### Sample size calculation

Sample size estimation for this study was based on the primary outcome of physical activity level measured in minutes and 77.8 min as between-group difference. A total of 214 participants (107 per group) will be needed based on analysis to reach the power of 90% with an alpha error of 0.05 and an estimated study dropout rate of 20%.

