### Statistical analysis

The obtained data will be analyzed using SPSS Statistics ver. 26.0 software (IBM Co., Armonk, NY, USA). The significance level will be set to 0.05. To compare differences between groups, both parametric and nonparametric tests will be adopted accordingly. Descriptive statistics for clinical variables and comorbidity levels will be presented as mean with standard deviation, and median with lower and upper quartiles. Logistic regression will be used to investigate factors associated with a worse long-term prognosis of TMD in terms of pain and function. All potential confounders, including clinical indices of TMD symptoms measured before treatment, body mass index, blood pressure and pulse rate, scores reflecting psychosocial status, sleep quality, and hematologic indices will be included as independent variables along with actigraphy data such as the amount of energy consumption per day, metabolic equivalent of task, steps count, sleep time, wake after sleep onset, sleep efficiency, sleep fragment index, and movement index. Factors will be added first in order to make adjustments, after which will be discarded consecutively one at a time with the first being the one with the highest *p*-value. The cutoff point of confounders to be discarded will be set as *p* < 0.250. If the *p*-value is 0.250 ≤ *p* ≤ 0.300, the confounder will not be discarded if this affects the OR by more than 10% [40]. Receiver operating characteristic (ROC) curves will be analyzed to explore thresholds for potential biomarkers. Their prognostic values will also be assessed by using Kaplan–Meier curve and both univariate and multivariate COX regression models. If the estimated sample size is not reached, multiple imputation will be used for missing data. A single overall analysis result will be produced by combining multiple analysis results.

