The current literature generally supports the fact that higher physical activity level is associated with lower systemic inflammation. CRP levels were more associated with the frequency of daily MVPA than the total accumulated time of weekly MVPA [64]. According to the National Health and Nutrition Examination Survey (NHANES), CRP levels were reversely associated with the amount of time spent engaging in leisure-time physical activity [65]. However, in British men, CRP levels were not significantly related to the amount of physical activity level [66]. It was concluded that the duration of physical activity does not seem to matter, and MVPA was considered to be more important. In a study using actigraphy, sedentary time was positively associated with greater CRP levels [67]. A randomized control trial compared CRP levels of participants physically active and inactive, and results showed lower CRP levels in the active group [68]. Also, CRP levels were positively correlated with longer sitting times. Such relations could also be found in populations with other diseases [69]. When it comes to individuals with arthritis, ≤ 150 min per day of MVPA or ≥ 4000 of daily step counts could be associated with lower hsCRP levels [70]. In fibromyalgia patients, 10–35 min of MVPA per day and 5000–9000 daily steps were associated with lower hsCRP levels [70].

The accumulating evidence supports the intimate relationship between physical activity, sleep quality, and systemic inflammation which are all factors known to influence TMD symptoms in previous literature [71–74]. Through this prospective study based on objective physical activity measurements in a well-defined patient group of TMD, the resulting data will be able to support the establishment of a clinical guideline related to physical activity recommendations and the diagnostic value of such measurements in TMD prognosis.

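### Objective 2 promises an activity cut-off that affects prognosis, but ROC, the only threshold method stated, cannot show that such a cut-off exists and locates it poorly at about 171 evaluable patients

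*Protocol article*

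**What the plan says.** All references are to the protocol article.

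- **Objectives, second item.** The effect of activity on treatment response is to be analysed "by determining the cut-off value for physical activity that affects treatment prognosis". The wording takes for granted that such a value exists. No method is named.
- **Statistical analysis, threshold method.** "Receiver operating characteristic (ROC) curves will be analyzed to explore thresholds for potential biomarkers". This is the only threshold-finding tool in the section. It is exploratory in tone and does not mention activity.
- **Statistical analysis, next sentence.** "Their prognostic values will also be assessed by using Kaplan–Meier curve and both univariate and multivariate COX regression models".
- **Statistical analysis, regression.** Logistic regression of poor prognosis is planned, with actigraphy measures (energy use, metabolic equivalents, steps) among the independent variables.
- **Sample size calculation.** "A total of 214 participants (107 per group) will be needed", for "power of 90% with an alpha error of 0.05", a difference of 77.8 min in activity between groups and 20% dropout. The calculation concerns a difference in mean activity, not the location of a cut-off.
- **Discussion, closing paragraph.** The data are expected to "support the establishment of a clinical guideline related to physical activity recommendations".

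**The concern.** The objective asks a question about the shape of a relation: is there an activity level at which prognosis changes, and where is it? An ROC analysis answers a different question, namely which split of the sample best separates patients with poor prognosis from the rest. Some split is always best. If risk falls smoothly with activity, the best split lies near the middle of the activity distribution and moves considerably by chance. If risk is unrelated to activity, a split is still returned.

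The article itself gives reason to doubt a simple threshold. Its Background reports that in fibromyalgia exercise goes with less pain but high-intensity exercise with more. Its Discussion cites favourable ranges of activity for an inflammatory marker in fibromyalgia patients (10–35 min per day, 5000–9000 steps), not one cut-point. If risk is raised at both ends, no single cut-off can represent it.

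At stake is whether Objective 2 is answered, and whether a figure in minutes or steps is later read as an established activity level when it is largely a product of the method and the sample.

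**Working it through.** **1. Evaluable number.** From Sample size calculation: 214 × (1 − 0.20) = 171.2, so about 171. Recruitment of cases gives a different total ("The final sample size is estimated to be approximately 200 participants"). That would leave 200 × 0.8 = 160, and precision would be no better.

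**2. The plan's own figure.** The SD is not given, so 214 cannot be reproduced from the stated inputs alone. It can be checked for consistency. With n per group = 2(z₁₋α/₂ + z₁₋β)² / d², two-sided 0.05, 90% power and d = 0.50:

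- n = 2 × (1.960 + 1.282)² / 0.25 = 84.1, rounded up to 85
- 85 / 0.8 = 106.25, rounded up to 107 per group, 214 in total

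A one-sided test with d = 0.45 also gives 85 and then 107. The stated total is therefore not shown to be wrong. The corresponding SD is about 156 min (two-sided) or 173 min (one-sided).

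**3. Where an ROC cut-off falls when no threshold exists.** Simulation with these assumptions, none of which the article states: n = 171; normally distributed activity score; binary poor prognosis in 30%; log-odds linear in activity; cut-off at the maximum Youden index. Percentiles refer to the activity distribution.

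| True relation | Mean AUC | Central 95% of cut-offs |
|---|---|---|
| No association | 0.50 | about 2nd to 97th percentile |
| Smooth, OR 1.5 per SD | 0.61 | about 14th to 81st |
| Smooth, OR 2.0 per SD | 0.68 | about 19th to 72nd |

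The widths at OR 1.5 and 2.0 are 81 − 14 = 67 and 72 − 19 = 53 percentile points. Repeated runs agree to about one point.

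**4. Sensitivity.**

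- *Event rate.* At OR 1.5, 20% events give the 12th to 81st percentile and 50% give the 17th to 82nd.
- *Direction.* If ROC may choose either direction, the no-association range is about the 10th to 88th.
- *A real threshold.* With a true step at the median (OR 3, base rate 30%), the range is the 30th to 66th. Even a genuine threshold is located only loosely.
- *Risk raised at both ends.* With log-odds 0.4x² and either direction allowed, mean AUC is 0.50 and the cut-off falls in one tail or the other (7th to 92nd percentile).

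**5. What the optimum looks like under no association.** A cut-off was returned every time. The mean apparent Youden index was about 0.10 with the direction fixed and 0.14 with either direction allowed, against a true value of 0.

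**The case against.** **The ROC sentence may not concern activity.** It speaks of potential biomarkers, a term the article otherwise uses for blood indices, and the objective names no method. This stands: a reader might infer that the plan promises to find the activity cut-off by ROC, and the text does not say so. But if ROC is not meant for activity, Objective 2 has no stated threshold method at all, and the mismatch between *determining* in the objective and *explore* in the analysis remains.

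**This is detail for an analysis plan.** The cut-off criterion, intervals and validation are commonly left there, and their absence from an article is no defect. What remains is the pairing of a stated objective with a stated method that cannot answer it.

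**Activity is already in the regression.** True, so its association with prognosis does not rest on ROC alone. As stated, those models do not ask whether a threshold exists, but they are the natural place to ask.

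**The instability is easily overstated.** This also stands, on three counts:

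- A reader might infer that the cut-off can fall almost anywhere. That fits no association or a weak trend. At OR 2.0 the range covers about half the distribution. With no association, an AUC interval covering 0.5 would usually warn the reader.
- A reader might convert the OR 1.5 range to nearly 300 min, or say that a repeat study would typically differ by hundreds of minutes. The conversion needs a back-solved SD, for which the article gives no sidedness and no time unit. Even with 157 min, two repeat studies at OR 1.5 differ by a median of only about 72 to 75 min, and about 7% of pairs differ by more than 200 min.
- A reader might infer that the cut-off would go straight into a guideline. The Discussion says only that the study's data can support one, and Patient grouping fixes a separate 150/75 min per week classification that does not depend on ROC.

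**Conclusion.** The point holds in a limited form. The objective presupposes a cut-off that affects prognosis, while the only stated threshold tool returns one whether or not it exists. With about 171 evaluable patients and a smooth relation, its location is uncertain over roughly half to two-thirds of the activity distribution at odds ratios of 2.0 and 1.5 per SD, and over nearly all of it with no association. A bare figure could therefore look firmer than it is when used to support advice on activity.

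These ranges rest on an assumed Youden criterion, 30% events and a smooth log-linear relation. They do not depend on the missing SD. That ROC is meant for activity is inferred. The sample size is not shown to be wrong. The change should be made, but the remaining analyses do not depend on it.

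**What to change.** 1. **Start from the regression already planned.** For Objective 2, keep actigraphy activity continuous and allow a non-linear relation with prognosis, for example by a spline.
2. **Test for a threshold.** Report a cut-off only if adding a threshold term improves the fit over the smooth relation. Because the location of the break is itself estimated, the comparison should allow for the search, for example by bootstrap.
3. **Label and qualify any ROC cut-off.** Present it as exploratory, with a bootstrap 95% interval for its location. If the interval spans most of the observed range, report the dose-response curve and state that no cut-off was identified.
4. **Reword Objective 2** to *assess whether a cut-off exists*. This also reconciles the objective with the exploratory wording of the analysis section.

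The cost is a change of wording and some computing, with no new data. The downside is small: the study may have to report that no single cut-off was found.

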#### Study outcomes

##### 3.1.6.1. Primary outcome measures: clinical outcomes listed below will be gathered at the participant’s first visit (baseline) and at 6- and 12-month post-treatment.

Amount of physical activity and sleep duration objectively measured using ActiGraph wGT3X-BT (ActiGraph, Florida, USA), a validated 3-axis accelerometer that includes ambient light sensors. Actigraphy is a method to monitor the cycles of rest and activity, which does not involve any invasive procedures. The movements of the accelerometer and light exposure can be continually recorded with a watch-like device worn on the wrist to objectively determine the amount of physical activity and sleep duration of a participant. Despite its limitations in measuring and staging sleep, actigraphy data provides real-life information on both the objective amount of physical activity and sleep by allowing the participant to maintain normal routines in his or her natural environment. Physical activity is measured at baseline only. (Fig. 1)*Amount of comfortable mouth opening* [12] the participant will be asked to open his or her mouth as wide as possible while remaining pain-free. If the participant is already experiencing pain, open as wide as possible without increasing current pain. Interincisal distance between the maxillary and mandibular reference teeth will be measured.*Amount of maximum mouth opening* [12] the participant will be asked to open as wide as possible, even if it is painful. Interincisal distance between the maxillary and mandibular reference teeth will be measured.*Muscle tenderness on palpation* [12] 12 masticatory muscle areas will be palpated on both sides including posterior, middle, and inferior temporalis muscle area and origin, body, and insertion of the masseter muscle with 1 kg of pressure.*Joint capsule tenderness on palpation* [12] 6 areas of TMJ will be palpated on both sides including the posterior, superior, and lateral parts of the capsule with 0.5 kg of pressure in a passive state. When palpation elicits subjective pain, the response will be recorded as positive. Joint noises are verified through palpation.*Subjective pain intensity* participant reported pain intensity based on a 0–10 numeric rating scale (NRS).

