## Trial status

The protocol is version 1.2 (June 24, 2021). The first recruitment began on July 21, 2021. Recruitment period ended on May 5, 2022. The participants will be followed for 12 months after their first intervention and this will be approximately February 25, 2023.

Data collection is in process. The trial submission was postponed due to delays in trial registration caused by the COVID-19 pandemic related working issues.

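### Kaplan–Meier and Cox are planned on outcomes seen only at 6 and 12 months, and the adjusted prognosis models use only binary outcomes

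*Protocol article*

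**What the plan says.** The primary outcome section sets the schedule: "clinical outcomes listed below will be gathered at the participant’s first visit (baseline) and at 6- and 12-month post-treatment". The clinical outcomes are comfortable and maximum mouth opening, muscle and joint capsule tenderness on palpation, and pain on a 0–10 scale. For mouth opening, "Interincisal distance between the maxillary and mandibular reference teeth will be measured". The Trial status section gives the length of observation: "The participants will be followed for 12 months after their first intervention".

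The Statistical analysis section names three kinds of analysis that bear on prognosis:

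- Group comparisons: "To compare differences between groups, both parametric and nonparametric tests will be adopted accordingly".
- Adjusted prognosis models: "Logistic regression will be used to investigate factors associated with a worse long-term prognosis of TMD in terms of pain and function".
- After ROC curves to explore biomarker thresholds: "Their prognostic values will also be assessed by using Kaplan–Meier curve and both univariate and multivariate COX regression models".

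The article describes no outcome whose onset date is observed between visits. It names no tie method and no method for interval-censored times.

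**The concern.** Kaplan–Meier and Cox assume that the time of each event is known, or nearly so. Here an event built on pain, mouth opening or tenderness can only be found at a visit, so its time is known to within six months. The survival curve would show the appointment calendar. The hazard ratio can be pulled toward 1, by an amount that depends on how ties are handled. A biomarker's prognostic value could then be understated, and results could differ between analysts who choose different tie options.

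The second part concerns information. The two kinds of adjusted prognosis model named, logistic and Cox, both need a yes/no outcome. Pain intensity and interincisal distance are quantitative and measured three times. If adjusted conclusions about prognosis rest only on a cut version of these measures, power is lost in the analyses that control for confounding, which the Background section treats as essential.

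**Working it through.** **The plan's own figure.** The Sample size calculation section gives 214 (107 per group) for a difference of 77.8 min of activity, 90% power, alpha 0.05 and 20% dropout. No SD is given, so the figure cannot be reproduced independently. It fits an SD of about 156 min with a two-sided test: n = 2 × (1.960 + 1.282)² × 156² / 77.8² = 84.5, so 85 per group; 85 / 0.8 = 106.25, so 107; total 214. From this I take only 85 evaluable per group. The calculation concerns activity minutes, not prognosis.

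**Where event times can fall.** There are two post-baseline visits, so an event is recorded at 6 or at 12 months and at no other time.

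**Effect on a Cox hazard ratio.** Assumptions: constant hazard h per month in one group and 2h in the other (true hazard ratio 2), equal groups, no dropout. The risk of a new event in each six-month interval is p0 = 1 − exp(−6h) and p1 = 1 − exp(−12h). These are the same in both intervals, so the Breslow score equation is solved in large samples by θ = p1/p0 = 1 + exp(−6h). Breslow therefore estimates a ratio of interval risks, not of hazards:

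- h = 0.015: 1 + exp(−0.09) = 1.91
- h = 0.03: 1 + exp(−0.18) = 1.84
- h = 0.06: 1 + exp(−0.36) = 1.70
- h = 0.12: 1 + exp(−0.72) = 1.49

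The complementary log-log model estimates log(1 − p1) / log(1 − p0) = 12h / 6h = 2 at every h.

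A simulation with 85 per group and 400 runs per row agrees (hazard ratio, with power in brackets):

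| Event by month 12 | Exact times | Breslow | Efron | Complementary log-log |
|---|---|---|---|---|
| 23% | 2.04 (56%) | 1.95 (51%) | 2.03 (55%) | 2.04 (55%) |
| 41% | 1.98 (80%) | 1.82 (70%) | 1.98 (81%) | 1.99 (81%) |
| 64% | 1.98 (94%) | 1.69 (84%) | 1.95 (92%) | 1.99 (92%) |
| 86% | 2.00 (98%) | 1.48 (71%) | 1.88 (98%) | 2.01 (98%) |

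A separate simulation gave Breslow values of 1.93, 1.88, 1.68 and 1.48. The spread at 41% (1.82 and 1.88, around the limit of 1.84) is simulation noise.

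**Cost of a binary outcome.** Take the standardised difference that gives exactly 90% power with 85 per group: d = (1.960 + 1.282) × √(2/85) = 0.497. Cut a normal outcome so that a chosen share overall is worse, and use power = Φ[(|p1 − p2| − 1.96 × s0) / s1], where s0 is the pooled and s1 the unpooled standard error:

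- Median split: 40.2% against 59.8%; (0.196 − 1.96 × 0.0767) / 0.0752 = 0.61, power 73%.
- Worst 30%: 21.5% against 38.5%; (0.170 − 1.96 × 0.0703) / 0.0691 = 0.47, power 68%.

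Restoring 90% would need 135 and 151 evaluable per group instead of 85.

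With baseline adjustment (171 participants, 0.5 SD, baseline correlation 0.5; 1,500 simulated trials), a linear model has 96% power. Baseline-adjusted logistic regression has about 80% at a median split and 75% for the worst 30%.

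**The case against.** Several points on the other side stand.

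- A reader might infer that the plan collapses every continuous outcome. It does not. The planned parametric and nonparametric group comparisons can use pain and mouth opening as measured, and a plain two-sample comparison keeps the 90% above. Palpation responses are recorded as positive, so those outcomes are not continuous to begin with. The loss concerns the adjusted prognosis models.
- A reader might infer that Cox on these data must be badly biased. With Efron ties the estimate stays near 2 unless most participants have the event (1.88 at 86%), and little power is lost. Even Breslow is mild when events are uncommon (1.95 at 23%).
- The survival models are attached to the potential biomarkers, after an exploratory ROC step. The article does not present them as the main analysis.
- The definition of a worse prognosis may sit in the full protocol or analysis plan, so its absence here is not counted.
- The 90% power in the article is for activity minutes. No power for prognosis is claimed, so none is contradicted, and the text does not show that the study cannot afford the loss.
- A binary outcome serves a stated purpose: the Objectives section seeks an activity cut-off that affects prognosis, and ROC curves need a binary state.

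A multiplicity charge might also be added. A familywise error rate for the several clinical outcomes would assume independent tests and is a separate question. It has no bearing on whether survival methods fit this schedule.

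None of this removes the mismatch. The visit schedule and the survival methods are both fixed in the article, and no event definition based on these outcomes would give more than two event times.

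**Conclusion.** The point holds in limited form. Kaplan–Meier and Cox do not suit outcomes observed at two post-baseline visits. With a true hazard ratio of 2, the Cox estimate ranges from essentially unbiased (Efron, up to about 41% with the event) to about 1.5 (Breslow, about 86%). A discrete-time complementary log-log model gives about 2.0 in every case, with power within about two points of exact times. These figures rest on an assumed hazard ratio, constant hazards, equal groups and a range of event rates; the article gives none of these.

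Separately, the adjusted prognosis models named use binary outcomes only. At a difference of about 0.5 SD, cutting the outcome lowers power from about 90% to 73% or 68% without baseline adjustment. The effect size and the cut-offs are assumptions. This is a reason to add a model for the quantitative outcomes. It does not show that the planned binary analyses are wrong or that the stated sample size fails.

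**What to change.** 1. Replace Kaplan–Meier and Cox with a discrete-time complementary log-log model, or an interval-censored model, for any binary endpoint. Report the proportion with the endpoint at 6 and at 12 months in place of a survival curve. Proportions by visit also show improvement followed by relapse, which a first-event analysis hides.
2. Beside the logistic model, add a baseline-adjusted linear or mixed model for pain intensity and mouth opening at 6 and 12 months, with the same confounders and activity measures.
3. Keep the binary logistic and ROC analyses for the cut-off objective. No redesign around a single primary model is needed for this point.

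The cost is a change to the analysis wording and a little more analysis work. No new data are needed and standard software suffices. The drawback is a display less familiar than survival curves.

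### Multiple imputation is tied to whether an ambiguous sample size is reached, not to whether data are missing, so on one natural reading the planned-for dropouts have no stated analysis method

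*Protocol article*

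**What the plan says.** The only analysis rule for missing data is in the article's Statistical analysis section: "If the estimated sample size is not reached, multiple imputation will be used for missing data". It is followed by "A single overall analysis result will be produced by combining multiple analysis results", which describes the pooling step. No method is given for the case where the size is reached.

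The size that the rule refers to appears twice. Recruitment of cases says "The final sample size is estimated to be approximately 200 participants". Sample size calculation says "A total of 214 participants (107 per group) will be needed", with "an estimated study dropout rate of 20" per cent.

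Three other statements bear on the point:
- Study outcomes places the clinical outcomes at baseline, 6 and 12 months, and physical activity at baseline only.
- Interventions says that staff will contact patients who miss a visit, and that the data of those who withdraw consent are left out of the final analysis.
- Statistical analysis names logistic regression as the method for factors linked to worse long-term prognosis.

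**The concern.** Bias from missing data depends on who is lost and why. Reaching a target number does not remove it, and falling short does not create it. A rule that applies imputation according to a count therefore attaches the remedy to the wrong condition. The same data could be analysed in two ways according to how the count is read, and that reading can be chosen after the data are seen.

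The long-term prognosis models are at stake, and they serve the study's main objectives. In a pain cohort, loss to follow-up may plausibly be related to improvement or persistence of pain, and to activity. The 20% allowance for dropout protects precision only. It was also attached to activity in minutes, which is measured at baseline, so it does nothing about missing 12-month outcomes.

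**Working it through.** **1. The plan's own figure.** Inputs from Sample size calculation: "physical activity level measured in minutes and 77.8 min as between-group difference", 90% power, alpha 0.05, 20% dropout, 214 in total. The standard deviation (SD) is not given, so 214 cannot be reproduced independently. Solving backwards with n per group = 2 × SD² × (1.960 + 1.282)² / 77.8², two-sided (sidedness is not stated):
- Inflating by 1/(1 − 0.20): SD of about 156 gives 85 per group; 85 / 0.80 = 106.25, rounded up to 107. The need before inflation is 2 × 85 = 170.
- Inflating by 1.20: SD of about 160 gives 89 per group; 89 × 1.20 = 106.8, rounded up to 107. The need before inflation is 2 × 89 = 178.

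The point does not depend on which was used, except in the last two rows of step 3.

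**2. Expected follow-up at 20% dropout.**
- 214 enrolled: 214 × 0.80 = 171.2 followed; 214 × 0.20 = 42.8, about 43, not followed.
- 200 enrolled: 200 × 0.80 = 160 followed; 40 not followed.

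**3. Is imputation triggered if 214 enrol and 20% are lost?**

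| Reading of the count | Comparison | Triggered? |
|---|---|---|
| Enrolled, against 214 or about 200 | 214 reaches both | No, with about 43 missing |
| Analysable, against 214 | 171 < 214 | Yes |
| Analysable, against about 200 | 171 < 200 | Yes |
| Analysable, against 170 before inflation | 171 ≥ 170 | No, by one patient |
| Analysable, against 178 before inflation | 171 < 178 | Yes |

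One dataset gives both answers. The article reports that recruitment has closed but not how many enrolled, so the reader cannot tell which case applies.

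**4. Possible effect on the prognosis rate (assumed values).** Suppose 30% truly do worse, with dropout of 40% among them and 11.4% among the rest. Overall dropout is 0.30 × 0.40 + 0.70 × 0.114 = 0.20. Complete cases show 0.30 × 0.60 / 0.80 = 22.5%. For a range, suppose 25% of completers do worse. If the rate among dropouts is 25%, 40% or 50%, the whole-cohort rate is 0.80 × 25% + 0.20 × that rate = 25%, 28% or 30%. Complete cases report 25% each time.

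**5. Possible effect on the odds ratio (assumed values).** The complete-case odds ratio (OR), inactive against active, equals the true OR × (retention in inactive-worse × retention in active-not-worse) / (retention in inactive-not-worse × retention in active-worse). Take a true OR of 2.0.
- Dropout by outcome alone, as in step 4: 2.0 × (0.60 × 0.886) / (0.886 × 0.60) = 2.0. No bias.
- Dropout by activity alone: the factors cancel in the same way. No bias.
- Dropout of 40% in inactive-worse, 20% in active-worse, 10% otherwise: 2.0 × (0.6 × 0.9) / (0.9 × 0.8) = 1.5.
- The same with 40% and 20% exchanged: 2.0 × (0.8 × 0.9) / (0.9 × 0.6) = 2.67.

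**6. Covariates (assumed values).** The models start with many variables. If 20 covariates were each missing independently in 1% of patients, 0.99^20 = 82% would be complete. With 20% dropout, 214 × 0.80 × 0.818 = 140 remain for a complete-case model.

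**The case against.** The strongest reply is that the text does not say imputation is used *only* in that case, and mentions neither enrolment nor complete cases. A reader might infer that 12-month outcomes certainly go unhandled once recruitment succeeds. The document does not support that. If the count means analysable patients, 171 is below both stated sizes and imputation would be used in exactly the planned-for scenario. This stands, and it limits the claim to an ambiguous rule tied to the wrong quantity.

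Other stronger readings also fail:
- **Imputation as a replacement for patients never recruited.** The sentence speaks of missing data, not of missing patients.
- **The 6-month data will be ignored.** The article does not say so. It also plans Kaplan–Meier and Cox analyses, which can keep patients until censoring, provided censoring is non-informative.
- **The 22.5% and the OR of 1.5 as expected errors that imputation would repair.** They rest on dropout rates with no source in the documents, and dropout there depends on the unseen 12-month outcome. Imputation under missing at random corrects this only as far as the observed data explain it. Conversely, if only outcomes are missing and dropout depends only on covariates in the model, the complete-case OR is already valid.
- **All 43 recovered.** Any dropouts who withdraw consent are excluded under Interventions and cannot be imputed.

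It may also be said that such detail belongs in an analysis plan that is not shown. That holds for the imputation model and the sensitivity settings. It does not hold for the trigger, which the article itself states.

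**Conclusion.** The concern holds in qualified form. The stated rule makes imputation depend on a count that does not govern missing-data bias and has no single meaning in the document. Read as enrolment, it leaves up to about 43 of 214 patients (20%) with no stated method, and the logistic models would by default use complete cases. Read as analysable patients against 214 or about 200, it would trigger imputation.

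The size of any bias cannot be derived from the document. The illustrations show only that it can matter: a prognosis rate of 22.5% against a true 30%, and an OR of 1.5 or 2.67 against a true 2.0. The OR results require dropout that depends on both activity and outcome. The protocol's planned sample size is unaffected.

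**What to change.** Delete the sample-size condition. State instead that missing follow-up outcomes and covariates will be multiply imputed under missing at random whatever number is reached. The imputation should use baseline covariates, activity and 6-month outcomes, and leave out patients who withdraw consent, as Interventions already requires.

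Report two sensitivity analyses: complete cases, and a missing-not-at-random analysis in which imputed outcomes are shifted by a range of amounts (delta shift). The second is needed because imputation corrects outcome-dependent dropout only in part. The imputation model and the shifts can be set out in the analysis plan, before the 12-month outcomes are analysed.

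The two stated sizes, about 200 and 214, should also be reconciled, although missing-data handling would no longer depend on them.

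The cost is one sentence in the protocol and a modest amount of extra analysis. No new data, added recruitment or change in patient care is needed.
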